### Risks and precautions during the study

1. Excerbation of clinical symptoms and suicide

For patients at any age with major depressive disorder, their disease may be possibly exacerbated, regardless of the administration of antidepressants, and they are likely to have suicidal ideation and suicidal behavior as well as abnormal change of behavior, and this risk may continue until the condition is significantly relieve. Depression is known to be associated with some mental disorders and suicide risk, and these mental disorders themselves are the strongest signs of suicide.

For all the subjects receiving the study drug (Ansofaxine Hydrochloride Extended Release Tablet or placebo) for treatment, exacerbation of their clinical symptoms, suicidal tendency and abnormal change in behavior should be closely observed, in particular in the initial stage of drug treatment.

When antidepressants are used for treatment of adult and pediatric patients with major depressive disorder, other psychotic or non-psychotic disorders, the following symptoms may appear: anxiety, agitation, panic attack, insomnia, irritability, hostility, aggression, impulsiveness, restlessness (psychomotor restlessness), hypomania and mania. Although the correlation of the occurrence of the above symptoms with exacerbation of depression and/or suicidal impulse has not been identified, these symptoms may be the foreboding of suicide.

For the subjects with persistent exacerbation of depressive symptoms, suicide or signs associated with it, discontinuation of study drug should be considered, in particular for those whose symptoms are severe, occur suddenly or newly appear.

In this study, the subjects with suicide risk should be excluded.

1. Prolonged QT interval

The in vitro study showed that Ansofaxine Hydrochloride could inhibit the potassium channel coded by hERG, however, no prolonged QT interval was seen overall in the animal study, nor clinically significant prolongation of QT interval was seen in the phase I clinical trial on tolerability. In order to ensure subject’s safety, subjects with clinically significant abnormality on ECG (in particular prolonged QTc interval) should be excluded, and will be monitored through ECG during the study.

1. Blood Pressure

It was observed in the pharmacological study on cardiovascular safety in Cynomolgus monkeys that this product could induce elevated blood pressure in the animals, however, no clinically significant change was seen in the blood pressure in the phase I clinical trial on tolerability. In order to ensure subject’s safety, effect of the drug on blood pressure should be noted during the clinical study. In this study, hypertensive patients with poor control of blood pressure should be excluded, and will be monitored through blood pressure in supine and orthostatic blood pressure at each visit.

# Adverse Events Reporting

Adverse event (AE) is defined as any unfavorable medical event that occurs in the subject who receives study drug in clinical trial, which does not necessarily have a causal relationship with the drug. In this study, adverse events (serious adverse event and non-serious adverse event) from the signature of informed consent form to the last visit will be recorded.

## AE record(s)

The adverse event record form should be filled in truthfully during the study. Its correlation with the study drug will be evaluated based on comprehensive consideration of complications and concomitant medications, through detailed record of its type, intensity, time of occurrence, duration, therapeutic measure and treatment.

All the physical examination and laboratory examination findings required in the study protocol should be recorded in the subject’s CRF. The physical examination and laboratory examination findings after administration will be compared with that prior to administration, the change must be evaluated as to judge if it meets the definition of adverse event if it is indicative of exacerbation of clinical status, and all the changes determined to meet the definition of adverse event will be recorded in Section Adverse event in CRF.

The medical document on adverse event should be recorded in the original document, including the laboratory examination report form.

## Criteria for severity assessment of adverse events

When filling in the Adverse event form in CRF, investigators will describe the intensity of adverse event with mild, moderate and severe. In order to unify the criteria, the intensity of event will be graded as below:

Mild: no interference with subject’s daily activities.

Moderate: interference to some extent with subject's daily activities.

Severe: serious interference with subject’s daily activities.

Attention should be paid not to confound severe adverse event with serious adverse event: severe is one category to measure the severity of an event, adverse event and serious adverse event can both be assessed as severe, all the events meeting the definition of serious adverse event should be listed as serious adverse event.

## Assessment criteria for the correlation between AEs and investigational product

The correlation with the study drug should be evaluated for all the adverse events, and the incidence will be calculated for definitely related,positively related, probably related and possibly related adverse reactions.

| Incidence of adverse reactions = | Number of subjects with at least one adverse reaction | × 100% |
| --- | --- | --- |
|  | Total number of subjects for evaluation of safety |  |

The judgment criteria for the correlation between adverse event and investigational product are seen in Table 2

Table 2 Assessment criteria for the correlation between AEs and investigational product

| Indicators | Results | | | | |
| --- | --- | --- | --- | --- | --- |
|  | Definitely related | Probably related | Possibly related | Possibly not related | Unrelated |
| The time of occurrence of the event coincides with the time of administration | ＋ | ＋ | ＋ | ＋ | ＋ |
| The adverse event is related with the known adverse reaction of the drug | ＋ | ＋ | ＋ | － | － |
| The adverse event can be explained with other reasons | － | － | ± | ± | ＋ |
| The adverse event is resolved following discontinuation of the drug | ＋ | ＋ | ± | ± | － |
| The adverse event reappear after dose resumption | ＋ | ？ | ？ | ？ | － |

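### Causality Table 2 has no category for an event that does not coincide with dosing, and cannot rate a known-type event as not related even when another cause explains it

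*Protocol*

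**What the plan says.** Section 9 of the protocol sets the collection window: adverse events "from the signature of informed consent form to the last visit will be recorded". Section 9.3 then requires a rating for each of them: "The correlation with the study drug should be evaluated for all the adverse events". It names Table 2 as the criteria for that judgement and defines the output: "the incidence will be calculated for definitely related,positively related, probably related and possibly related adverse reactions". The denominator is the number of subjects evaluated for safety.

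Table 2 has five questions and five categories:

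| Question | Definitely | Probably | Possibly | Possibly not | Unrelated |
|---|---|---|---|---|---|
| 1. "The time of occurrence of the event coincides with the time of administration" | + | + | + | + | + |
| 2. "The adverse event is related with the known adverse reaction of the drug" | + | + | + | − | − |
| 3. "The adverse event can be explained with other reasons" | − | − | ± | ± | + |
| 4. "The adverse event is resolved following discontinuation of the drug" | + | + | ± | ± | − |
| 5. "The adverse event reappear after dose resumption" | + | ? | ? | ? | − |

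Section 9.1 separately tells the investigator to judge causality in the light of complications and concomitant drugs. The Safety Analysis part of section 11.2 makes the safety evaluation descriptive and tabulates all adverse events by type, severity, frequency and relationship.

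**The concern.** A causality table should let bad timing, or a clear alternative cause, argue against the drug. Here row 1 never does, because 'Unrelated' itself demands coincident timing. Row 2 closes both not-related columns to any event of a known type, however good the alternative explanation.

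Both gaps will be met in practice. Adverse events are recorded at Visits 1 and 2, before any double-blind dose. The reactions seen in phase 1 (section 1, Clinical Pharmacology) are non-specific: nausea, vomiting, diarrhea, dizziness and weakness. The trial's own scales list overlapping symptoms: diarrhea and general weakness in HAM-D17 (Appendix 1), and nausea, vomiting, diarrhea and vertigo in HAMA (Appendix 3). Such events with another explanation can be expected in all arms.

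At stake is the meaning of the adverse-reaction incidence, a defined output of a trial whose secondary objective includes preliminary safety as a basis for the next phase.

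**Working it through.** The protocol states no figure on this point, so there is nothing to reproduce. The check is an enumeration of Table 2.

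**Enumeration.** Each of the five questions is answered + or −, which gives 2^5 = 32 patterns. An entry of ± or ? is read as accepting either answer.

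| Timing | Known type | Patterns | Columns that fit |
|---|---|---|---|
| + | + | 8 | 'Possibly related' in all 8, a stronger grade as well in 2; a not-related column in none |
| + | − | 8 | 'Possibly not related' in all 8, 'Unrelated' as well in 1; a related column in none |
| − | + or − | 16 | none |

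Three results follow.

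1. All 16 patterns with non-coincident timing fit no column. A screening event, or a wash-out event judged against the double-blind drug, must be rated but has no category.
2. The pattern timing +, known type +, other cause +, resolution −, recurrence − fits only 'Possibly related' and is counted.
3. Among the 16 ratable patterns, row 2 alone decides whether the event is counted. This works in both directions. An event of a new type with coincident timing, no other cause, resolution on stopping and recurrence on re-dosing fits only 'Possibly not related' and is left out.

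Leaving row 5 unanswered (16 patterns) does not change this: 8 fit no column, 4 fit only related columns and 4 fit only not-related columns.

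**Possible effect on the rates (all rates are assumptions).** Let b be the background rate of known-type events that are counted as reactions, and d the drug-caused rate, acting independently. Then placebo = b, active = b + d(1 − b), and difference = d(1 − b). Assume that half of the background meets the pattern in result 2 and could be rated 'Unrelated'.

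- As written, b = 20%: placebo 20%; active 0.20 + 0.10 × 0.80 = 28% to 0.20 + 0.20 × 0.80 = 36%. Ratio 1.4 to 1.8, difference 8 to 16 points.
- After correction, b = 10%: placebo 10%; active 0.10 + 0.10 × 0.90 = 19% to 0.10 + 0.20 × 0.90 = 28%. Ratio 1.9 to 2.8, difference 9 to 18 points.

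The change in the difference is d × b/2. With d = 10% to 20%, that is 0.25 to 0.5 point at b = 5%, 1 to 2 points at b = 20%, and 2 to 4 points at b = 40%. In an arm of 52, one point is 0.52 subject.

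**Check of the repair.** Setting timing and known type to ± under 'Unrelated', with the other three entries kept, makes that column fit 2 × 2 = 4 of the 32 patterns. One is the pattern in result 2. Two have non-coincident timing, so 16 − 2 = 14 such patterns still fit no column and depend on the pre-dose rule. Setting both rows to ± under 'Possibly not related' instead would make that column fit all 32 patterns, because its other entries are already ±, ± and ?.

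**The case against.** The best defence is that Table 2 is not meant to be applied mechanically. Section 9.1 asks the investigator to weigh complications and concomitant drugs, and one who does so may rate nausea during gastroenteritis as unrelated. The site may also record gastroenteritis itself as the event, so that row 2 becomes −. This carries some weight, but section 9.3 calls Table 2 the judgement criteria and nothing lets section 9.1 override it. An investigator who follows 9.1 to 'Unrelated' for a known-type event contradicts the table, and sites may resolve the conflict differently.

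It is also fair to say that little inference depends on this. Safety is descriptive, all-cause tables do not use the rating, and no stated rule ties dose choice to the adverse-reaction rate. That stands and limits the point.

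Three stronger readings are tempting, and the documents do not support them.

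- *Events that began before dosing are counted as adverse reactions.* 'Possibly related' also requires coincident timing, so the table leaves these events without a category; it does not count them.
- *The adverse-reaction rate adds nothing to the all-event table.* Events not of a known type remain not related, and a known-type event with another cause cannot reach 'Probably' or 'Definitely'. The two outputs still differ.
- *The contrast between doses and placebo is materially diluted.* No rate in the protocol supports a size. In the illustration the ratio moves visibly, but the difference moves by 1 to 2 points at a 20% background. The exclusion of new-type events is a second error, so no net direction can be claimed.

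**Conclusion.** The point holds for the table as written. An event whose timing does not coincide with dosing cannot be classified, although collection starts at consent and every event must be rated. A known-type event on treatment with another cause, no resolution on stopping and no recurrence on re-dosing is forced into 'Possibly related' and counted in every arm. Whether a ratable event is counted depends on known type alone.

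These conclusions rest only on a literal reading of Table 2, with ± and ? accepting either answer. The consequence is confined to the descriptive adverse-reaction incidence and the relationship tables. The size of any dilution is not known from the documents. The table should be corrected, but the efficacy analysis and the all-cause safety tables are unaffected.

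**What to change.** - In Table 2, under 'Unrelated', set timing to ± and known type to ±. Keep + on other cause and − on resolution and recurrence.
- State that an event meeting that pattern is rated 'Unrelated' in preference to 'Possibly related', because both columns will accept it when timing and known type are +.
- State that an event starting before the first double-blind dose is 'Unrelated' to double-blind drug. This is needed because the column change alone covers only 2 of the 16 non-coincident patterns. Section 7.2 also calls the wash-out tablets study drug, so the rule should name the double-blind drug explicitly. Say as well which category takes any other event that does not coincide with dosing.
- Do not set both timing and known type to ± under 'Possibly not related'. That column would then accept even a known reaction that resolves on stopping and recurs on re-dosing.
- Reconcile Table 2 with section 9.1, saying which governs when they differ, and with the 'positively related' grade in section 9.3, which has no column in the table.

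These edits do not bring new-type events into the count; that limit should be stated beside the adverse-reaction incidence. The cost is one corrected table and a few sentences in the protocol and the case report form guide. The small downside is somewhat more investigator judgement for known-type events.

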Compared with the administration under fasted state, the T_max_was prolonged, C_max_was elevated and relative bioavailability was about 106% for *O-*demetylvenlafaxin in healthy subjects, after oral administration of Ansofaxine Hydrochloride Extended release Table 120 mg following meals.

1. Evaluation of the tolerance and pharmacokinetics of single dose vs. multiple doses of ansofaxine hydrochloride extended-release tablet in healthy volunteers in a randomized,double-blind,placebo-controlled,dose-escalation study.

A total of 48 male and female healthy volunteers were enrolled in this trial, including 40 subjects receiving Ansofaxine Hydrochloride Extended release Table orally and 8 subjects receiving placebo. 24 case-times of adverse events occurred in 15 volunteers receiving Ansofaxine Hydrochloride Extended release Table, including a total of 16 case-times of adverse events possibly related with the study drug, the common related adverse events were 5 case-times of nausea, 3 case-times of vomiting and 3 case-times of diarrhea, the other related adverse events also included 2 case-times of dizziness, 2 case-times of elevation of total bilirubin and 1 case-time of elevated alanine aminotransferase, the majority of them were mild in intensity and spontaneously relieved without treatment. No clinically significant change related with the study drug was seen in vital signs, physical examination, 12-lead ECG and blood oxygen saturation. The study results showed a good safety and tolerability for oral Ansofaxine Hydrochloride Extended release Table once per day for consecutive 7 days, in the dose range of 40~160 mg.

Results of the study on Ansofaxine Hydrochloride Extended release Table after orally multiple doses showed the median T_max_ was 3~6 h, mean t_1/2_was 9.09~10.04 h, the systemic exposure was mildly increased in each dose group and the accumulation factor was about 1.20, in the dose range of 40~160 mg/day. The plasma concentration of ODV could reach steady state after consecutive administration for three days. The steady-state C_max_ and AUC of ODV were dose proportional.

This clinical trial was conducted in accordance with the clinical trial approval letter issued by China Food and Drug Administration (CFDA) on June 16, 2015 (approval letter number: 2015L01158/2015L01159/2015L01160/2015L01161).

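### Table 2 keeps any event that is not an already known reaction out of the adverse-reaction incidence, however strong the other causal evidence

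*Protocol*

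**What the plan says.** Protocol section 9.3 states that "the incidence will be calculated for definitely related,positively related, probably related and possibly related adverse reactions". The numerator is "Number of subjects with at least one adverse reaction" and the denominator is the number of subjects evaluated for safety. Causality is judged by Table 2. Its second row reads "The adverse event is related with the known adverse reaction of the drug"; in the summary below it is called known reaction, and the other row labels are likewise shortened.

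| Row | Definitely | Probably | Possibly | Possibly not | Unrelated |
|---|---|---|---|---|---|
| Timing fits dosing | + | + | + | + | + |
| Known reaction | + | + | + | − | − |
| Other explanation | − | − | ± | ± | + |
| Resolution on stopping | + | + | ± | ± | − |
| Recurrence on restarting | + | ? | ? | ? | − |

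Four other places bear on the point:

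- Section 9.1 asks for a comprehensive assessment that takes account of complications and concomitant medication.
- Section 9.4 continues follow-up after study end for unresolved events that are related to the product.
- Section 9.5 requires serious adverse events to be reported whatever their relationship.
- The Safety Analysis part of section 11.2 tabulates type, severity, frequency and relationship for all adverse events.

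**The concern.** Whether a reaction is already known should support a causal judgement, not be a condition for it. Table 2 uses ± and ? elsewhere for criteria that need not be met, but gives this row a firm sign in every column. The clinical experience reported in the protocol comes from healthy volunteers. The only repeated-dose study ran for 7 days, "including 40 subjects receiving Ansofaxine Hydrochloride Extended release Table orally and 8 subjects receiving placebo". The present trial treats patients for 6 weeks, so some reactions may well appear for the first time.

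At stake are three things that depend on the causality label: the adverse-reaction incidence of section 9.3, the relationship column of the adverse-event tables in section 11.2, and follow-up after study end under section 9.4. An incidence that omits unlisted reactions by rule is biased downwards in any arm where they occur.

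**Working it through.** The protocol gives no figure to reproduce, so the check is a reading of Table 2 followed by an enumeration.

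**Step 1: what separates counted from uncounted.** The incidence counts possibly related and above, so the boundary lies between the third and fourth columns. Row by row, possibly related against possibly not related reads: timing + and +; known reaction + and −; other explanation ± and ±; resolution ± and ±; recurrence ? and ?. Known-reaction status alone decides whether an event at the boundary is counted.

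**Step 2: enumeration.** Fix timing at +. Let known reaction, other explanation and resolution each be + or −, and recurrence be +, − or not known. That gives 2 × 2 × 2 × 3 = 24 patterns, of which 12 have known reaction −. Read ± as either answer. The protocol does not define ?, so both readings were tried.

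| 12 patterns with known reaction − | ? read as any answer | ? read as not known |
|---|---|---|
| Definitely, probably or possibly related | 0 | 0 |
| Possibly not related | 12 (one also fits unrelated) | 4 |
| Unrelated only | 0 | 1 |
| No column fits | 0 | 7 |

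The contribution of unlisted reactions to the incidence is therefore zero under both readings.

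**Step 3: the strongest case.** Take an event with no other explanation that resolves on stopping and recurs on resumption. If it is a known reaction, it fits definitely related. If it is not, it is possibly not related when ? means any answer, and fits no column when ? means not known.

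**Step 4: exceptions.** Sections 9.1 to 9.5 and the Safety Analysis contain no exception for unlisted events. The comprehensive assessment in 9.1 may soften practice but does not alter the table.

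**Step 5: the obvious one-cell repair.** If the known-reaction entry for possibly related is changed to ± and nothing else changes, every pattern that fits possibly not related also fits possibly related, because no other row differs. The repair needs a new separator.

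**The case against.** The strongest objection is that detection of new reactions does not run through this ratio. A reader might infer from Table 2 that new reactions would go unseen in this trial. The protocol does not support that. The safety variable is adverse events, recorded from consent onwards; all of them are tabulated; events leading to withdrawal and serious events are noted separately; and serious events are reported whatever the causality. An unlisted reaction appears in those tables, with the wrong relationship label. Nor is the ratio named in the Safety Analysis or the synopsis, or stated to be the basis for choosing a dose. All of this stands and limits the consequence.

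A reader might also attach a number of patients. With zero events in n subjects, the one-sided 95% upper limit is 1 − 0.05^(1/n). For the 40 repeated-dose volunteers this is 7.2%. For all 60 + 12 + 40 = 112 on active drug (assuming different people in the three studies) it is 2.6%. Applied to 4 × 52 = 208 drug-treated patients, these give 208 × 0.072 = 15.0 and 208 × 0.026 = 5.4. They are not estimates of the bias, for three reasons:

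- They are ceilings for one hypothetical reaction never yet seen.
- They take known to mean seen in this drug's own studies. The protocol does not define the word, and it may include reactions of ODV, the active metabolite to which the doses are matched in section 4.2.
- The numerator counts subjects, so a patient who also has a known reaction is already in it.

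Two oddities in 9.3 might be read as further bias. Timing is + in every column, so an event before dosing fits none; but such an event should not count as a reaction, and it does not. Positively related has no column in Table 2, so it adds no subjects. Neither changes the incidence.

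What the objection does not reach is the rule itself. Complete adverse-event tables do not correct the adverse-reaction incidence, the relationship column or the scope of follow-up in 9.4.

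**Conclusion.** The point holds in limited form. Read as written, Table 2 and the counting sentence give any event that is not a known reaction a contribution of exactly zero to the adverse-reaction incidence. Such an event also does not count as related for follow-up after study end. The harm is confined to the incidence, the relationship tabulation and that follow-up. The direction of the bias is downwards; its size cannot be derived from the protocol, because known is undefined and the frequency of unlisted reactions is not given. The conclusion assumes that investigators apply Table 2 as the judgement criteria, which is what 9.3 says. It does not depend on how ? is read. The rule is worth correcting because it gives a wrong result in a stated safety summary and is cheap to repair.

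**What to change.** 1. In Table 2, change the known-reaction entry under possibly related from + to ±.
2. Keep the two middle columns apart through the other-explanation row. Enter + for possibly not related, and add a note that an event which is not a known reaction is possibly related only when no other reason explains it. A known reaction with another possible explanation stays possibly related, as now.
3. State that ? means any answer. Otherwise 7 of the 12 unlisted patterns, including the strongest, still fit no column. With this reading, the 6 unlisted patterns without another explanation become possibly related. The 6 with one remain possibly not related (one of them also fits unrelated, as before).
4. State that the by-arm comparison of treatment-emergent adverse events regardless of causality is the main safety comparison, and that the adverse-reaction incidence is supportive.
5. Delete positively related from the counting sentence, as an editorial correction.

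The cost is wording in the table and the CRF guidance, plus re-rating under blind of any events already assessed. The reported adverse-reaction incidence becomes somewhat higher, because unlisted events with no other explanation now count, including some that the drug did not cause. An unlisted event still cannot rise above possibly related, but that is enough for it to be counted.
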